#### Intervention adherence

Interventionists of both treatment conditions will be introduced during a seminar of four days, perform training sessions with two pilot patients from their study site within the next 4 months and subsequently attend a repetition seminar of two days. Methods of the seminar are presentations, role-plays and feedback rounds on role-plays of each interventionist. Experts in relearning in AD from Nijmegen will give two separate seminars for the ELL and TEL arm.

In both seminars interventionists will be instructed in

1. understanding the pool of the 20 IADL tasks

2. how to involve patients in selecting two relevant tasks of daily living from the pool of IADL tasks

3. how to invite the patient to perform the task

Interventionists of the **ELL **group and the substitutes will additionally learn

1. how each task is pre-structured in steps and how to give cues for these steps

2. how to anticipate possible errors of the patient before they occur and how to intervene and again give cues so that the patient is motivated to continue.

Interventionists of the **TEL **group and the substitutes will additionally learn

1. how to intervene when errors occur so that the patient is motivated to continue.

Seminars will be at different time points, in order to prevent contamination of specific seminar content between the ELL and TEL group. Two treatment manuals with detailed instructions will be provided, separately for the ELL and the TEL intervention.

Each interventionist of the ELL and the TEL condition and each substitute interventionist must apply 12 sessions to two pilot patients. The third and tenth relearning session with each pilot patient must be video recorded. The Dutch supervisors will use these video tapes to assess the quality of the treatment and to reflect on possibilities for improvement within the repetition seminar. Interventionists will receive certification based on the quality of their pilot treatment and their contribution within the repetition seminar. In order to monitor the treatment adherence during the study phase, the main ELL and TEL interventionist must provide video tapes with two tasks of the third and tenth relearning sessions with their first patient. The focus of the treatment adherence will be the interventionists' anticipation of and reaction on the patient's errors. Criteria will be specified in the treatment manuals. In cases of inappropriate treatment adherence the interventionist will receive an intensive telephone mentoring session. Continuing insufficient adherence will lead to the interventionist's replacement.

### Outcome

The primary outcome is the performance of the two selected and trained daily living tasks. The applied measurement is the Task Performance Scale. It demonstrated feasibility and responsiveness within the pilot trial. The evaluation of task performance by measuring the number of occurring errors or the number of insufficient task performances is an established standard in trials on relearning cognitive or daily living tasks. Patient's task performance will be video recorded by the interventionist, in order to assure blinded rating and to avoid that the patient will have potentially confusing contacts with several different persons. Blinded assessors from the REDALI-DEM headquarters in Freiburg will rate the videos regarding the number of occurring errors and steps performed insufficiently. Table 2 shows the primary and the secondary outcomes including measurement instruments and time points. Secondary outcome and control measures are performed by the study physician during the patient's visit at the study site, except the Verbal Rating Scale for the satisfaction with the intervention, which is applied by the interventionists at the patient's home.

**Table 2 T2:** Measurement scheme including primary and secondary outcome

Weeks	0		11		16*		19-20		26
Measurement time points	t_0_		t_1_		t_2_				t_3_
Intervention		12 sessions		break		break	refresher	break	
Primary outcome									
Task Performance Scale (Rating of assessment video)	x		x		**x**				x

Secondary outcomes									
Satisfaction with intervention (Verbal Rating Scale)		each session					each session		
Activities of daily living (Interview for Deterioration in Daily Living Activities in Dementia)	x				**x**				x
Resource utilisation (Resource Utilisation in Dementia)	x				**x**				x

Control measurements									
Cognition (Mini Mental State Examination)	x				x				x
Course of Dementia (Clinical Dementia Rating)	x				x				x
Challenging behaviour (Neuropsychiatric Inventory, 12 items questionnaire)	x				x				x
Socio-demographic data	x								
Depression (Geriatric Depression Scale, 15 items)	x								
Attention (Trail Making Test)	x								
Intervention adherence (rating of treatment videos)		selected sessions							

* Primary measurement time point

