### Statistical analysis

Baseline measures and demographics of participants significantly differing at baseline in ELL and TEL group as well as control measures are used as co-variates in an analysis of variance. The primary intention-to-treat analysis will be compared with a per-protocol analysis.

The method "Last Observation Carried Forward" will not be used for the imputation of missing data, because it introduces bias in dementia research [20]. If necessary, the Full Information Maximum Likelihood method will be applied for data replacement [21,22]. Drop-out analysis will be performed comparing all baseline and control measurements and follow-up data of participants and dropouts as far as sufficient data are available. Therefore participants are asked to give consent to a final assessment using the Task Performance Scale at the dropout time point. Furthermore, the carers are asked to fill in the Interview for Deterioration in Daily Living Activities in Dementia at all measurement time points as planned.

The comparison of ELL and TEL group will be adjusted for baseline imbalance and process variations. Variations in treatment integrity, medication of achetylcholinesterase inhibitors, and study sites will be considered as possible mediating variables and analysed with hierarchical linear models. All statistical tests will be two-sided on an alpha level of 0.05.

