### Ethical Considerations

In the trial and error condition, individuals will benefit from the trial and error learning, but will be exposed to the risk of experiencing deficits through insufficient task performances more frequently than individuals in the errorless condition. For cases where these experiences lead to severe behavioural disturbances the trial will be discontinued. If the ELL intervention proves to be superior to the trial and error learning, the errorless learning approach will reduce the experience of insufficient task performances in AD patients. In all cases, the closest caring relative of the patient will be asked to give assent to support the trial procedures by filling in forms and arranging appointments. Patients who are not able to consent will be included, if a legally appointed representative gives consent.

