### Monitoring

Relevant Standardised Operating Procedures (SOP, http://www.tmf-ev.de/Produkte/SOP.aspx) will be adapted to the specific requirements of the REDALI-DEM study.

SOP-pre-visit: to ensure the reliable evaluation of recruitment capacity and competence of staff at each site

SOP-monitor-visit: to ensure the reliable data collection and transfer and appropriate query management at each study site

SOP-data-check: to ensure identical procedures, when incoming data are checked for correctness and queries are handled

SOP-data-entry-check: to ensure a rate of data entry errors of less than 0.2%

SOP-adverse-event: to ensure that adverse events are disclosed early and handled appropriately

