### Safety

No evidence suggests that the application of learning strategies causes medical or mental instability in AD population. A trial steering committee will be constituted of two persons from the applicant group and one independent person with following responsibilities. (1) Statistician: supervision of statistics and assessment adherence monitoring. (2) Principal investigator from the Nijmegen research group: supervision of treatment adherence monitoring. (3) Professor in ethics: ethical judgement of the study protocol and possible adverse events. Severe adverse events are defined as non-elective hospital admissions or death. Adverse events will be reported according to the standards of Good Clinical Practice.

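### Control measures enter the model as covariates with no limit to baseline, so week-16 NPI could adjust away a possible treatment effect, and the article states no between-arm NPI comparison

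*Protocol article*

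**What the plan says.** Ethical Considerations describes a risk that differs by arm. Patients in the trial-and-error arm "will be exposed to the risk of experiencing deficits through insufficient task performances more frequently than individuals in the errorless condition". The same section goes on: "For cases where these experiences lead to severe behavioural disturbances the trial will be discontinued".

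Table 2 (Outcome) separates the primary outcome, the secondary outcomes and the control measurements. The row "Challenging behaviour (Neuropsychiatric Inventory, 12 items questionnaire" stands in the third group and is marked at weeks 0, 16 and 26. Week 16 is the primary time point.

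Statistical analysis gives the control measures two uses. First, after naming baseline variables that differ between arms, it adds "as well as control measures are used as co-variates in an analysis of variance". Second, "Drop-out analysis will be performed comparing all baseline and control measurements and follow-up data of participants and dropouts".

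On harms, the Safety section says "Severe adverse events are defined as non-elective hospital admissions or death" and, separately, "Adverse events will be reported according to the standards of Good Clinical Practice". The Monitoring section lists "SOP-adverse-event: to ensure that adverse events are disclosed early and handled appropriately".

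**The concern.** A covariate measured after randomisation is harmless only if treatment cannot affect it. The article itself gives a route by which TEL could affect behaviour: more frequent failure, then disturbance. If week-16 NPI is in the primary model, the arm contrast no longer estimates the full effect of allocation on task performance. Any part of the effect that runs through behaviour is removed. If behaviour and performance share unmeasured causes, the remaining contrast can be biased as well.

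The second consequence concerns what the trial reports. The results are meant to inform guidance on how to instruct people with memory impairment. The Sample Size reasoning justifies looking for small effects partly because the intervention is considered low in risk. Randomised data that bear on that premise are collected, but the only uses stated for them do not compare the arms.

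**Working it through.** **1. Does the text confine control measures to baseline?**

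- The covariate sentence names baseline measures and demographics that differ at baseline, then adds control measures as a further class. The baseline qualifier is attached to the first class.
- In Table 2, three control measurements are taken only at week 0 (socio-demographic data, depression, attention). Three are repeated at weeks 0, 16 and 26 (MMSE, Clinical Dementia Rating, NPI). One, intervention adherence, is rated on selected treatment sessions and so has no baseline value. The class as a whole is therefore not a baseline class.
- The same section later adjusts the comparison for process variations as well as baseline imbalance, so variables arising after randomisation are not excluded in principle.

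Use of week-16 NPI is thus permitted by the text, but not stated.

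**2. What would adjusting for week-16 NPI do?**

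Let δ be the difference between arms in week-16 NPI, and β the within-arm slope of the Task Performance Scale on week-16 NPI, given the other covariates. Then, in a linear model:

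adjusted contrast = total treatment effect − β × δ.

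The shift is zero only if δ or β is zero. The document gives neither, so the shift cannot be sized. If TEL raises the NPI and a higher NPI goes with worse performance, the adjustment shrinks a true advantage of ELL.

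**3. Is a between-arm NPI comparison stated anywhere?**

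- Secondary outcomes and secondary research questions: behaviour is not listed.
- Drop-out analysis: it compares participants with dropouts, not ELL with TEL.
- Adverse events: reported to Good Clinical Practice standards, with no mention of the NPI.

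No such comparison is stated.

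**4. What could the planned data show?**

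The article gives no figure for the NPI. The number per arm is taken from its sample size, which reproduces: λ = f² × N × m / (1 − r) = 0.01 × 160 × 2 / 0.4 = 8.00; critical F(1, 158) = 3.901; power 0.803. With 1:1 allocation, 160 / 2 = 80 per arm.

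In units of the NPI standard deviation, with complete data:

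- Unadjusted 95% half-width: 1.96 × √(2/80) = 1.96 × 0.158 = 0.31 SD.
- Adjusted for baseline NPI: multiply by √(1 − r²). The value r = 0.6 is borrowed from the sample size calculation for the primary outcome and is an assumption for the NPI.

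| assumed r | √(1 − r²) | half-width (SD) |
|---|---|---|
| 0.4 | 0.917 | 0.28 |
| 0.6 | 0.800 | 0.25 |
| 0.8 | 0.600 | 0.19 |

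For 80% power, two-sided 5%, the detectable difference is (1.96 + 0.84) × 0.158 = 0.44 SD unadjusted, and 0.44 × 0.8 = 0.35 SD at r = 0.6. The estimate would be informative about moderate differences and weak for small ones.

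**The case against.** The strongest reply is that much of this rests on silence in a condensed article. A reader might infer that the arms will never be compared on behavioural harm. The article does not support that: adverse events in general are to be reported to Good Clinical Practice standards, a procedure for them is listed, and tables of adverse events and discontinuations by arm are the kind of detail left to a full protocol or analysis plan. This part of the reply stands, so the absence of a discontinuation table is not held against the plan.

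A reader might also infer that the severe adverse event definition shuts behavioural disturbance out. It sets the severe category, not the limit of what is reported, and a disturbance leading to a non-elective admission would fall inside it. Nor is it exact to say that the NPI serves only as a covariate, since control measures also enter the drop-out analysis, though not by arm. And it would be wrong to say that the plan does enter week-16 NPI; the time point is simply left open.

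Further, behaviour is not among the research questions, so classing the NPI as a control measure is a consistent design choice. Patient experience is not ignored either: satisfaction is a secondary outcome rated at each session. Finally, the NPI at weeks 16 and 26 may miss distress during sessions. The plan for dropouts names a final Task Performance Scale and continued carer ratings of daily living, but not the NPI.

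These points narrow the concern but leave its core. The covariate role is something the article states, not something it omits, and it is stated without a time restriction for a variable that the article's own reasoning says treatment may change.

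**Conclusion.** The point holds in a limited form. The covariate rule is fixed badly: it allows a post-randomisation NPI value, measured at the primary time point, into the primary comparison. That could bias the contrast by β × δ, an amount the document does not allow one to compute. Separately, no ELL-versus-TEL comparison of the NPI is stated, although one could be had from planned data with a 95% half-width of about 0.31 SD, or 0.25 SD at an assumed baseline correlation of 0.6 (0.28 to 0.19 SD for correlations of 0.4 to 0.8).

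These widths describe what could be learned; they do not measure an error in the plan. They assume 80 patients per arm with complete NPI, and would widen with missing data. The conclusion about the covariate rule depends on none of these figures.

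**What to change.** In Statistical analysis, state that the NPI and the other repeated control measures (MMSE and Clinical Dementia Rating) are used as covariates in the treatment comparison at their baseline values only.

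Add that the difference in NPI between ELL and TEL at weeks 16 and 26, adjusted for baseline NPI, will be reported with a 95% confidence interval as a descriptive safety or secondary comparison. State how many patients per arm have the NPI at each time point, and note that values may be missing for patients who discontinue, who may be those most affected.

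The cost is a change in analysis wording and one table, with no new measurement. The drawback is one more secondary comparison, which should be read as estimation and not as a further test of efficacy.

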### Sample Size

A sample size of 160 subjects (λ = 8.00, critical F = 3.901, numerator df = 1, denominator df = 158) is needed for the detection of small effects size (f = 0.10) in an analysis of variance with two groups and two repeated measurements at baseline and week 16 hypothesising an alpha of 5%, a power of 80% and a correlation of 0.6 between the measurement points.

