## Methods/Design

To compare the effects of errorless and trial and error learning, we used a seven-centre single-blind, active-controlled design with a 1:1 randomisation for two parallel groups. The study has been registered at the German Trial Register (No. DRKS00003117, available at http://apps.who.int/trialsearch). The Medical Ethics Committee of the University Hospital Freiburg has given ethical approval (No. 194/11).

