#### Reasoning

The sample size of the Nijmegen pilot study was small (N = 12) [19]. Powerful within-subjects analyses revealed high effect sizes in post-treatment (η^2^_p _= 0.8, p < 0.01) and delayed assessment (η^2^_p _= 0.5, p = 0.01). In order to avoid bias from carry-over effects between the groups potentially occurring in a within-subjects design, in the present trial a between-subjects design will be conducted and the interaction effect between groups and measurement points T_0 _(Baseline) and T_2 _(16 weeks after baseline) will be analysed as primary endpoint. The between-subjects design will reduce the statistical power, consequently more subjects are needed. Furthermore, the correlation of r = 0.85 between the measurements in control and treatment groups as stated in the meta-analysis of Kessels et al. is quite large [18]. However, they excluded trials with between-subjects design and only analysed studies using within-subjects design. Considering that group differences might be influenced by several unknown confounders in our real-life setting at the patient's home we assume a correlation of r = 0.6 for the power calculation. Although the meta-analysis demonstrated large effect sizes (d = 0.87), it also found large confidence intervals (CI95% = 0.10-1.64). It is assumed that detecting even small effects is reasonable, because the implementation of relearning techniques will be a low-cost and a low-risk intervention. For these reasons, we performed a conservative power calculation, which is able to detect even small effect sizes for the interaction. The patients' planned trial flow is shown in Figure 1.

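### The primary test is a change-score comparison; always adjusting for the baseline Task Performance Scale would raise power from 80% to about 88% under the protocol's own inputs, at no extra data cost

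*Protocol article*

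**What the plan says.** The Sample Size section of the protocol article bases the calculation on "an analysis of variance with two groups and two repeated measurements at baseline and week 16", with "an alpha of 5%, a power of 80% and a correlation of 0.6 between the measurement points" and an effect size of f = 0.10. It gives 160 subjects, λ = 8.00 and a critical F of 3.901 on 1 and 158 degrees of freedom. The Reasoning subsection then fixes the primary comparison: "the interaction effect between groups and measurement points T_0 _(Baseline) and T_2 _(16 weeks after baseline) will be analysed as primary endpoint". It presents r = 0.6 as an assumption, lowered from the 0.85 reported in a meta-analysis of within-subjects studies, and gives no range.

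Table 2 shows that the Task Performance Scale is rated at baseline (t0) and at week 16 (t2).

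The Statistical analysis section brings in two kinds of covariate: baseline measures and demographics that differ significantly between arms, and the control measures. Table 2 lists the control measures separately, and the Task Performance Scale is not among them. The section also says that the comparison will be adjusted for baseline imbalance, and it names Full Information Maximum Likelihood for missing data where needed. No sentence makes the baseline Task Performance Scale a covariate regardless of the baseline comparison.

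**The concern.** In a randomised two-arm trial with one baseline and one primary follow-up, the group-by-time interaction F test is the square of the t statistic comparing mean change between arms. It subtracts the baseline with a fixed coefficient of 1. ANCOVA estimates that coefficient from the data, so apart from one degree of freedom it is not less precise in large samples.

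The covariate rule does not close the gap. How much precision the baseline score adds depends on its correlation with the week-16 score, not on whether the arms happen to differ at baseline. Under the rule as written, a well-balanced baseline score would stay out of the model. The primary estimator would also switch with the result of a baseline significance test.

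At stake are some avoidable loss of power and more dependence than necessary on an assumed correlation. Validity is not at stake.

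**Working it through.** **Inputs.** From Sample Size: f = 0.10, r = 0.6, α = 0.05, power 80%, N = 160. From Statistical analysis: two-sided tests. From Methods/Design: 1:1 allocation. Assumed, because the documents give no SDs: equal SDs at T0 and T2, relaxed in step 4.

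**1. Reproduce the protocol's figure.** For the 2 × 2 interaction, λ = f² × N × 2 / (1 − r) = 0.01 × 160 × 2 / 0.4 = 8.00. The critical F(1, 158) is 3.901 and power is 80.3%. All stated values are reproduced.

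**2. Express it as a change-score test.** With SD 1 at each time, the variance of change is 2(1 − r), so λ = δ² × N / [4 × 2(1 − r)]. Setting this equal to the expression in step 1 gives δ² = 16f², so δ = 4f = 0.40 SD. Check: 0.16 × 160 / (4 × 0.8) = 8.0.

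**3. Same difference, ANCOVA on T0.** The residual variance is 1 − r² = 0.64, so λ = 0.16 × 160 / (4 × 0.64) = 10.0. With 1 and 157 df, power is 88.2%. The variance ratio is (1 − r²) / [2(1 − r)] = (1 + r)/2 = 0.80. ANCOVA reaches 80% power at N = 128 (λ = 0.16 × 128 / (4 × 0.64) = 8.0).

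Power at N = 160 and δ = 0.40 SD, equal SDs:

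| r | Interaction (change) | ANCOVA on T0 | (1 + r)/2 |
|---|---|---|---|
| 0.4 | 63.1% | 78.3% | 0.70 |
| 0.5 | 71.0% | 82.7% | 0.75 |
| 0.6 | 80.3% | 88.2% | 0.80 |
| 0.7 | 90.1% | 94.1% | 0.85 |
| 0.85 | 99.6% | 99.8% | 0.925 |

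**4. Relax equal SDs.** Let k = SD(T0)/SD(T2), with δ = 0.40 of the T2 SD. The change variance becomes 1 + k² − 2rk, while the ANCOVA variance stays 1 − r². At r = 0.6:

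- k = 0.8: change variance 1 + 0.64 − 0.96 = 0.68, λ = 6.4/0.68 = 9.41, power 86% against 88%.
- k = 0.6: change variance 1 + 0.36 − 0.72 = 0.64, the same as ANCOVA, so both have 88%.

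The 8-point gain therefore belongs to the equal-SD case. At r = 0.6 it shrinks as k falls from 1 to 0.6, where it vanishes.

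**The case against.** The strongest reply is that nothing here is stated wrongly. The sample size matches the named test, the arithmetic reproduces, and the interaction test is valid and unbiased under randomisation. The trial reaches its stated 80% under its stated assumptions, and the abstract plans for 175 patients rather than 160. The only empirical correlation in the documents is 0.85, at which the choice of test hardly matters. The analysis section also plans covariates, so the final analysis may not be the bare interaction test. All of this stands, and it limits the point to an improvement. What it does not supply is a sentence that always puts the baseline Task Performance Scale in the primary model.

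Two stronger readings are tempting.

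- A reader might infer that r must be low because tasks are chosen for failure at baseline, which would narrow the T0 range. The Intervention sessions section requires only that the patient cannot do the tasks without errors. That removes error-free performers and says nothing about the spread among the rest. If the range were narrowed, k would fall below 1 and the gap would mostly shrink: at r = 0.3 it is 57% against 75% with equal SDs, 65% against 75% at k = 0.8, and 71% against 75% at k = 0.6.
- A reader might infer that below r = 0.5 the planned test is worse than ignoring baseline. That holds only for equal SDs. In general, 1 + k² − 2rk exceeds 1 when r < k/2, so the threshold is 0.40 at k = 0.8 and 0.30 at k = 0.6. The documents give no SDs from which to place it.

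**Conclusion.** The point holds as a free improvement. The protocol fixes a change-score test as primary and leaves adjustment for the baseline score to a data-dependent rule. At the protocol's r = 0.6 with equal SDs, the interaction test carries 80% of the information that ANCOVA would use, which is 80% against 88% power at N = 160. A fall in r from 0.6 to 0.5 costs the interaction test about 9 points and ANCOVA about 5 to 6.

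The size of the gain rests on two things that the documents do not establish: the true correlation and the ratio of the SDs at T0 and T2. It could be about 2 points (k = 0.8, r = 0.6) or negligible (r = 0.85, equal SDs). The documents do not support calling the sample size wrong, the test invalid or the trial underpowered.

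**What to change.** State the primary analysis as a regression of the week-16 Task Performance Scale on arm, with the baseline Task Performance Scale always included as a covariate, whatever the baseline comparison shows. An equivalent likelihood model with baseline as covariate would serve as well and is consistent with the Full Information Maximum Likelihood method already named. Report the arm difference at week 16 with its 95% confidence interval. Keep N as planned, and show power over a range of r (for example 0.4 to 0.85) with the assumed SDs stated.

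The cost is one degree of freedom and a change to the analysis wording. No new data and no extra patients are needed, since the scale is already rated at both time points.
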